## Methods

### Study design and participants

The study is a randomised, single-centre, controlled, non-inferiority trial conducted in the Child and Adolescent Psychiatry Department of the Robert Debre University Hospital in France (protocol version n°1.2 02182020). This unit provide specialised treatment for children and adolescents with EOAN. The study protocol was approved by local ethics committee (ID-RCB: 2019–102408-49, CPP: 19.09.12.56704). Trial is also registered on ClinicalTrials.gov (NCT04479683).

Participants will be aged from 8 to 13 years inclusive at inclusion with diagnosis of anorexia nervosa according to DSM 5 criteria [12], requiring full time IP according to the French guidelines [13, 14] and affiliated to the French social security system. Only participants with no prior hospitalisation in a specialised eating disorder care unit will be eligible after informed consent of the holder(s) of parental authority.

Patients with other eating disorder (Avoidance/Restrictive Food intake Disorder or Eating disorders not otherwise specified according to DSM 5 criteria [12]), underlying unbalanced somatic diseases (in particular chronic inflammatory bowel disease, dysthyroidism, diabetes, adrenal insufficiency, diabetes insipidus, hemopathies, brain tumours, tuberculosis) will be excluded. We will also exclude children with contraindication to outpatient care due to indication of maintain IP for other reasons according to French guidelines (either with a psychiatric indication for continued hospitalisation such as severe suicidal ideations or with environmental indications for continued full-time hospitalisation (absence of family to accompany ambulatory care or impossibility due to distance)) [13].

### Procedure (Fig. 1)

**Fig. 1 Fig1:**
[figure not shown]
Study flowchart

At initial clinical assessment, eligible children and caregivers will be informed of the study and study protocol is fully explained by the investigator. After signature of the informed consent by the holder(s) of parental authority, target weight for weight normalisation will be calculated and participants will be randomised into one of the two trial arms. Weight normalisation is individualised and will be determined at inclusion and before randomisation to return to the previous BMI growth trajectory and is calculated by two different investigators [15–18].

Randomisation will be done by a randomisation list with the nQuery Advisor and nTerim 4.0 software implemented in the eCRF. Children and parents are informed of the result of the randomisation by the investigator.

After inclusion and randomisation, participants will be managed in 3 phases:

*period 1: *Full-time IP until somatic stabilisation (see below for definition); *period 2:* DP or IP according to their randomisation arm until weight normalisation is reached; *period 3:* OP follow-up.

*Period 1: *Full-time IP—identical for all included children- ongoing until somatic stabilisation, which is defined as: BMI over the 3^rd^ percentile, disappearance of somatic severity criteria for undernutrition such as bradycardia (heart rate below 40 per minute during sleep time or below 50 per minutes during day time), persistent disturbances of the biological balance (hypoglycaemia, hypophosphoremia, haemolysis, cytolytic hepatitis, elevated creatine kinase), or any somatic or biological manifestation requiring constant surveillance in hospital with usual medical, dietary and psychological care (persistent refusal to drink or eat, lipothemia, hypothermia). The treatment provides multi-disciplinary care for the child and his/her family as described in French guidelines [14], including:Child follow-up of AN and psychiatric comorbidities by a senior psychiatrist on a bi-weekly basisEndocrinologic and somatic evaluation by a senior endocrinologic paediatric for initial assessment M6 and M12 and by a psychiatrist resident for follow-up during IP and by a general practitioner during OPNutritional monitoring with a bi-weekly dietetic follow-upPsychological follow-up with weekly family therapyTherapeutic education for the child with a weekly psychoeducation group and day-care nurse follow-up

We will target a rapid weight gain from 500g to 1.5kg a week depending on the tolerance [19].

*Period 2: *At the end of the first period, patients start to receive treatment according to their randomisation arm until the weight normalization is reached. *For the control group*, full-time IP is continued as described in period 1 with additional cognitive remediation weekly group and weekly individual cognitive-based therapy until the weight normalisation is reached. During this time period, IP patients can benefit from permission to go home twice a week on Wednesday afternoons and weekends. *For the experimental group*, participants are discharged from IP and switch to DP one day per week until weight normalisation is reached.

The standardized DP treatment combines a medical assessment by a senior psychiatrist, family oriented treatment (parents' group and multi-family therapy session), a psychoeducation group, a cognitive remediation group, a dietetic follow-up with therapeutic meals and body constants monitoring (heart rate and blood pressure). Patients in the experimental group can return to their school activities and home life. During this period, the number of individual cognitive-based therapy sessions out from the hospital will be reported. If absence of weight gain leading to a BMI < 3rd percentile or weight loss of more than 10% of body weight during DP, patient will be readmitted to full-time IP until the weight normalisation is reached.

*Period 3: *After weight normalisation is reached, all patients will be provided the same OP follow-up until 12 month with a psychiatric consultation every month for 3 months and then once every 2/3 months as proposed in usual care.

Clinical, biological and psychometric assessments are done at baseline, at somatic stabilisation, at reaching weight normalisation, at 6 months and 12 months following study inclusion.

### Measures (Table 1)

**Table 1 Tab1:** Overview of measures and time of assessment

Assessment	Inclusion	Stabilisation	Weight normalization	6 months	12 months
*Clinical assessment weight, height, BMI *	x	x	x	x	x
tanner stage	x			x	x
*Nutritional markers* prealbumin, leptin, total ghrelin and IGF1	x		x		x
*Radiology* Bone mineralization (dual-energy X-ray absorptiometry) Bone maturation (en face radiograph of the left wrist)	x				x
*Global psychosocial* CGI	x		x	x	x
*Eating symptomatology* EDI-c, MRS	x		x	x	x
*Anxiety and depressive symptomatology* CDI, STAIC	x		x	x	x
*Self-esteem Scale* Rosenberg	x		x	x	x
*Motivation to change* HAQ-11S, Motivation questionnaire	x		x	x	x
*Treatment acceptability and quality of life* CSQ-8, SF-12	x		x	x	x
Resource consumption		x	x	x	x

#### Primary outcome

The primary non-inferiority outcome is BMI (Weight in kg/(Height in m^2^)) at 12 months after inclusion to assess non-inferiority on BMI maintenance.

#### Secondary outcomes

*Biological and radiological outcomes* will be collected. *Nutritional status* will be assessed with prealbumin, leptin, total ghrelin and IGF1. Body composition and *bone mineralisation* will be estimated by using dual-energy X-ray absorptiometry (DEXA, GE Lunar ProdigyCorp., Madison. WI). Bone mineral measurements will be expressed as standard deviation score according to age and sex (SDS). *Bone maturation* will be assessed from an en face radiograph of the left wrist, interpreted using the Greulich and Pyle atlas.

*Global clinical and psychological evaluation* will be assessed with the *Clinical Global Impression* (CGI) [20] scale. CGI is scored on a two-part 7 response levels evaluating illness severity (CGI-S) and improvement (CGI-I) from 1 (“not ill”/ “very much improved”) to 7 (“extremely ill”/ “much worse”).

*Eating disorder symptomatology* will be assessed with the *Morgan and Russell scale* (MRS) [21] and the *Children Eating Disorders Inventory* (EDI-c) [22, 23]. The MRS is a questionnaire designed to evaluate the long-term evolution of the eating disorder and is used to assess the main aspects of anorexia nervosa over a six-month period. A version has been adapted for younger children, with deletion of non-appropriated items as "menstruation", "psychosexual functioning" and "emancipation". The assessment of the adapted procedure has 8 subscales divided into 3 groups: Eating; Mental status; Socioeconomic Status.

The EDI-c is adapted form of the EDI for children from 8 years of age onwards [22, 23]. This is a multidimensional self-questionnaire that assesses different psychological, behavioural and emotional characteristics associated with eating disorder symptoms. It comprises 91 items divided into 11 factors: Drive for Thinness, Bulimia, Body Dissatisfaction, Low Self-Esteem, Personal Alienation, Interpersonal Insecurity, Interpersonal Alienation, Interoceptive Deficits, Emotional Dysregulation, Perfectionism, Asceticism, and Maturity Fears. Each of the 91 items is rated from 'never' to 'always', respectively from 0 to 3 for direct items and from 3 to 0 for indirect items.

*Depressive and anxiety symptomatology* will be respectively assessed by the Children Depression Inventory (CDI) [24], the *State –Trait Anxiety Inventory for Children* (STAIC) [25]. The CDI is a self-adapted Beck Depression Inventory for children aged 7 to 17 years, with 27 items scored from 0 (absent or normal behaviour for age) to 2 (severe). The total score, calculated as the sum of all the items, varies from 0 to 54 with a pathological threshold of 15. It is a widely used tool in the international literature to assess the intensity of depression.

The STAIC is a self-questionnaire and comprises two 20-item subscales, the Trait Anxiety and the State Anxiety. The scores observed for the two subscales range from 20 to 80, with a score of 35 or less corresponding to very low anxiety and a score of over 65 corresponding to very high anxiety.

*Self-esteem will be assess by the Rosenberg Self-esteem Scale * [26]* is* a self-questionnaire with a 10-items measure of global self-esteem, widely used in general and clinical populations. The higher the scores, the better the self-esteem. It can be used from the age of 8 years.

*Therapeutic alliance/perception of treatment benefit and Motivation to change* will be assessed by the *Helping Alliance Questionnaire-11* (HAQ-11S) [27], the *Consumer Satisfaction Questionnaire* (CSQ-8) [27] and the *Motivation Questionnaire* [28].

The CSQ-8 is a self -"satisfaction"-questionnaire, defined here as a concept tending to assess whether the needs of the consumer of a service are being met or not. In medical terms, patient satisfaction is an internationally recognized measure for the evaluation of the perception of quality of care; this dimension can have an influence on the outcome and adherence to the proposed treatment and thus on the acceptability of the treatment. It consists of eight questions, each with four response options ranging from one "not at all satisfied" to four "completely satisfied".

The HAQ-11S is a self-questionnaire of 11 items measuring the strength of the collaboration between the patient and the healthcare team.

The Motivation Questionnaire will assess the importance of change and the perceived ability to change. It consists of two questions: "How important is it for you to change" and "How confident are you in your ability to change". Both questions are rated on a Likert scale from 0: "Not at all" to 10: "Completely".

*Quality of life* will be assessed by the *Short-Form 12-Item Health Survey* (SF-12) [29, 30]. The SF-12 is a generic self-assessment scale of quality of life and a shortened version of the SF-36 validated in France. It contains 12 questions. It provides two scores: a physical health and a mental health summary scores. These two scores were constructed so that their average in the general population is 50 and range from 0 to 100, 100 indicating the highest level of quality of life.

*Social functioning* will be particularly evaluated based on the subscales of the MRS assessing the socioeconomic status: relationship with family, social contacts outside family, social activities and scolarity.

*Direct and indirect costs* will be calculated from resources consumption: all hospital admissions will be recorded as ambulatory consultations, complementary examinations, medical transport and number of non-working days for parents due to medical care for their child for control and experimental groups will be recorded.

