## Background

Early-onset anorexia nervosa (EOAN) is characterised by disease onset in children before the age of 13 years old and will thus include prepubertal and post pubertal onset [1]. Compared to the classic adolescent form of anorexia nervosa (AN), EOAN presents clinical and epidemiological specificities [1]. Children with EOAN more often present severe restrictive forms with more rapid weight loss, associated with a greater frequency of total aphagia and the presence of associated "non-specific" somatic symptoms (digestive complaints, abdominal pain) [2–4]. Frequently requiring inpatient treatment, children with EOAN also have a higher average length of stay (LOS) than adolescents with AN [1]. Despite an increased prevalence [5] and a specific burden in pediatrics and mental health departments, treatment knowledge remains sparse, and based on mainstream clinical opinion with little empirical standing [6]. In clinical practice, in children with AN, whereas experts recommend outpatient treatment (OP), in-patient treatment (IP) remains frequently indicated due to acute medical instability [6] or for those who have not improved with OP. Long LOS, social isolation, and elevated costs have led to discuss different treatment options with age-appropriate strategies for child population [6, 7].

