#### Statistical analysis plan

The statistical analysis of the data will be performed using an intention-to-treat analysis, all patients allocated to the control group or experimental group will be analysed. The descriptive analysis for each group at each assessment time will be expressed as number (percentage) for categorical variables, and as mean (SD) or Median [IQR] according to their normal or non-normal distribution for quantitative variables. As described above, the primary outcome for non-inferiority analysis is based on the comparison of the BMI at 1 year after inclusion between the two groups with a two-sided 95% confidence interval. Experimental strategy will be considered as non-inferior if the confidence interval upper limit of the difference in BMI between the 2 groups is less than 1 kg/m^2^ (non-inferiority margin) with a 0.025 alpha risk. The comparative analysis between the 2 groups for the primary or secondary criteria will be carried out using the appropriate tests: Chi^2^ test or Fisher's exact test for qualitative variables; Student's t test or non-parametric Wilcoxon test for quantitative variables, according to their normal or non-normal distribution. To determine prognosis factors associated with positive response to stepped-care model of DP after short IP, a regression model will be used to search for factors associated with the effect of the intervention, integrating the MRS score as the explained variable, and the CGI score, the HAQ11 and motivation questionnaire scores, and the severity of the weight deficit as explanatory variables.

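### Unadjusted tests are named for bone maturation, IGF1 and leptin although their inclusion values and Tanner stage are collected: an avoidable loss of precision, not a bias

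*Protocol article*

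**What the plan says.** All references are to the protocol article.

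- **Secondary outcomes.** For bone mineral the scale is given: "Bone mineral measurements will be expressed as standard deviation score according to age and sex (SDS"). For skeletal maturity the article names only the reading method; the outcome "will be assessed from an en face radiograph of the left wrist, interpreted using the Greulich and Pyle atlas". Nutritional status "will be assessed with prealbumin, leptin, total ghrelin and IGF1". No scale, transformation or reference standard is given for bone maturation or for these markers.
- **Statistical analysis plan.** "The comparative analysis between the 2 groups for the primary or secondary criteria will be carried out using the appropriate tests". For quantitative outcomes these are "Student's t test or non-parametric Wilcoxon test for quantitative variables, according to their normal or non-normal distribution". No covariate is named for any between-arm comparison.
- **Study design and participants; Background.** "Participants will be aged from 8 to 13 years inclusive at inclusion", and the condition "will thus include prepubertal and post pubertal onset".
- **Table 1.** Bone maturation is measured at inclusion and 12 months. The nutritional markers are measured at inclusion, weight normalisation and 12 months. Tanner stage is recorded at inclusion, 6 and 12 months.
- **Objectives (Background).** Non-inferiority is to be shown for biological outcomes too. The only margin stated is 1 kg/m2, for BMI.

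**The concern.** One development-dependent outcome is referenced to age and sex; its neighbours in the same section are not. An atlas reading of the wrist gives a bone age, which by construction follows chronological age. IGF1 and leptin can be expected to vary with age, sex and puberty; the article does not say so, and it is taken here as an assumption. Inclusion spans 8 to 13 years and both sides of puberty, so much of the between-child spread at month 12 may be ordinary development, which an unadjusted test leaves in the error term.

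Interval width is what matters here, because the objectives claim non-inferiority on biological outcomes. A wide interval gives little support to such a claim. With no margin stated for these outcomes, there is also a risk that a non-significant test is read as showing no harm. The variables that would remove much of the spread are already collected, but no stated between-arm comparison uses them.

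**Working it through.** **The plan's own figure.** The article gives no figure for these outcomes, only a sample size for BMI (margin 1 kg/m2, SD 1.35, one-sided 2.5%, power 90%). The normal approximation gives 2 × (1.960 + 1.282)² × 1.35² / 1² = 38.3, so 39 per arm. With the noncentral t, power is 0.898 at 39 and 0.905 at 40 per arm, so 40 per arm (80 in total) reproduces. The stated 88 is 80 × 1.1. Nothing below changes this.

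**Inputs for the check**

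| Input | Value | Source |
|---|---|---|
| Evaluable children per arm | 40 | Sample size section |
| SD of age | 0.8 to 1.73 years | Assumed; 1.73 = 6/√12 is a uniform spread from 8 to just under 14 |
| SD of bone age minus chronological age | 1.0 year (range 0.8 to 1.3) | Assumed |
| Correlation of that deviation, inclusion to month 12 | 0.8 to 0.9 | Assumed |
| IGF1 rise over ages 9 to 15 | 2- to 3-fold, log-linear | Assumed |
| IGF1 within-age SD, log scale | 0.35 | Assumed |

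**Bone maturation.** Half-width of the 95% CI = 1.99 × SD × √(2/40) = 0.445 × SD.

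1. Bone age in years: SD = √(age SD² + 1.0²).
   - Age SD 0.8: √(0.64 + 1) = 1.28, half-width 0.57 year.
   - Age SD 1.73: √(2.99 + 1) = 2.00, half-width 0.89 year.
2. Bone age minus chronological age: SD 1.0, half-width 0.45 year.
3. As in 2, also adjusted for the inclusion value: SD = 1.0 × √(1 − r²).
   - r = 0.8: SD 0.60, half-width 0.27 year.
   - r = 0.9: SD 0.44, half-width 0.19 year.

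The variance ratio of step 1 to step 2 is 1.28² = 1.64 at age SD 0.8 and 2.00² = 4.0 at age SD 1.73. If the deviation SD also runs from 0.8 to 1.3, the half-widths are 0.50 to 0.96 year (step 1), 0.36 to 0.58 (step 2) and 0.16 to 0.35 (step 3).

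For a true 1-year difference and deviation SD 1.0, power (two-sided 5%) on bone age in years falls from 0.94 to 0.61 as the age SD goes from 0.8 to 1.73. On bone age minus chronological age it is 0.99.

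**IGF1.** With age uniform over the six years, the log-scale variance due to age is (ln fold)²/12.

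- 2-fold: 0.693²/12 = 0.040; inflation 1 + 0.040/0.35² = 1.33; interval wider by √1.33 = 1.15.
- 3-fold: 1.099²/12 = 0.101; inflation 1 + 0.101/0.35² = 1.82; interval wider by √1.82 = 1.35.

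No figure is offered for leptin, since nothing in the article supports one.

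**Is there bias?** In 20,000 simulated trials with no treatment effect (40 per arm, age uniform over 8 to 14, deviation SD 1.0), the unadjusted comparison of bone age had a mean difference of 0.00 and a type I error of 0.051. The chance difference in mean age between arms has an SD of 1.73 × √(2/40) = 0.39 year (0.18 at age SD 0.8). Bone age in years carries that over, but the standard error already allows for it.

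**The case against.** Four points can be made for the plan.

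- **The analysed scale is not stated.** A reader might infer that raw bone ages and concentrations go into the tests. The article does not say so. An atlas reading is often set against chronological age, and a condensed article may leave the derived variable to the full protocol or analysis plan. This stands: silence on scale alone is no finding. What the article does fix is the family of unadjusted tests, and the unused inclusion values follow from that whatever the scale.
- **The tests are valid.** A reader might infer that normal development swamps or biases the treatment contrast. Allocation is randomised, and the simulation shows no bias and a nominal type I error. This stands: the only cost is precision.
- **No interval can be called too wide.** A reader might conclude that the intervals cannot support the non-inferiority objective. Without a margin for bone maturation, IGF1 or leptin that cannot be judged. This stands.
- **The size depends on an unknown age distribution.** The four-fold variance ratio for bone age holds only at an age SD of 1.73; at 0.8 it is 1.6. This stands, so the range is given. Subtracting age alone still leaves a half-width of 0.45 year; the further gain comes from the inclusion value and rests on the assumed correlation.

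**Conclusion.** The point holds as an avoidable loss of precision on secondary outcomes. The article references only bone mineral to age and sex, and names unadjusted tests for every quantitative secondary outcome, while collecting the covariates that would sharpen the comparison.

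On the central assumptions, moving from an unadjusted comparison of bone age in years to one that accounts for age and the inclusion value cuts the half-width from 0.57–0.89 year to 0.19–0.27 year. If the full protocol already uses bone age minus chronological age, the remaining gain is from 0.45 to 0.19–0.27 year. For IGF1, age alone would widen the interval by about 15% to 35%. All SDs, the correlation and the IGF1 gradient are assumptions; the article gives none of them.

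Severity is minor. The comparisons are unbiased and keep their alpha, and the primary outcome and sample size are unaffected.

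**What to change.** In the Statistical analysis plan section, replace the two-group test for these outcomes by a linear model at month 12 with arm, the inclusion value of the same measure, age, sex and inclusion Tanner stage. Report the adjusted difference with its 95% CI.

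In the Secondary outcomes section, state the analysed scale:

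- bone maturation as bone age minus chronological age on the day of the radiograph;
- IGF1 as an age- and sex-referenced score, or on the log scale if no suitable reference exists for the assay;
- leptin on the log scale.

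If the full protocol or analysis plan already fixes the scale, only the model needs adding. With age and the inclusion value in the model, most of the precision gain for bone maturation is obtained even on bone age in years; the subtraction mainly makes the descriptive tables interpretable.

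The cost is analysis wording only. Table 1 already has these measures at inclusion and month 12, so no visit, assay or patient is added.
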